#### Strategies to improve adherence to interventions {11c}

Participants are required to attend the study site in person to receive the intervention, and any missed sessions are recorded to monitor adherence. To improve adherence, appointment times are flexible between 8am and 6pm each day (room and staff availability permitting), are not required to be at the same time of day and are not required on weekends. To allow flexibility for long weekends, illness or other factors that prevent attending on site, a window of +3 days is tolerated between intervention sessions, with up to 1 additional week (maximum 5 weeks) tolerated to complete the 20 sessions. Free and accessible parking is provided on site. Participants will be reimbursed for time and travel with a $100 voucher at the end of the intervention period.

#### Relevant concomitant care permitted or prohibited during the trial {11d}

Participants are permitted to take current disease-modifying therapies/medications and physical rehabilitation treatment as usual during the trial, except for medications specifically listed under eligibility criteria and criteria for discontinuation sections. Treatment history, concomitant medications at baseline and any changes to medications will be recorded daily during the intervention.

#### Provisions for post-trial care {30}

At the end of the trial, participants will return to usual care of their treating neurologist. If participants suffer adverse or serious adverse events as a result of the trial, they will be treated in the public health care system. The University of Tasmania (UTAS) will provide insurance and indemnity, including legal liability to pay damages as a result of any claim or claims made against the UTAS, a protected person or affiliate during the protection period in consequence of clinical trials.

### Outcomes {12}

#### Primary outcomes

The primary outcome will be the incidence of treatment emergent adverse events (AE) and serious adverse events (SAE), recorded at each visit during the intervention phase. Incidence will be compared between rTMS and sham using the proportion of participants that had at least one AE against participants who experienced no AEs (each participant counted once). AEs leading to premature discontinuation from the study intervention and serious treatment-emergent AEs will be presented either in a table or a listing. A clinically acceptable difference between the rTMS and sham conditions in treatment emergent events is 10% for adverse reactions and 0% for suspected unexpected serious adverse reactions (SUSARs). We defined this clinically acceptable difference based on previously reported rates of the most common side effects in sham-controlled rTMS clinical trials for depression, which were headache (mean incidence rates of 16% sham vs. 28% rTMS; 12% difference) and scalp pain/discomfort (mean incidence rates of 15% sham vs. 39% rTMS; 24% difference) [25]. Clinical trials using rTMS for depression typically deliver higher intensity and longer duration stimulation, so we expect lower incidence rates of these common adverse reactions. Risk of serious adverse reactions is reduced by excluding participants who are potentially at higher risk of serious adverse reactions to rTMS (e.g. history of seizure) [14, 15].

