#### Intervention phase (visits 1–20) (~15min per day)

Upon arrival each day, participants will be asked to confirm their personal details (name and date of birth) and will be asked if they are experiencing any symptoms that are out of the ordinary. Participants will attend 20 sessions over a period of 4 consecutive weeks. A tolerance of +3 days will be allowed for weekends, sickness or inability to attend a session. Sessions will continue until 20 sessions are complete or up to a maximum of 5 weeks, whichever comes sooner. AEs and any concomitant medication changes will be recorded daily.

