#### Remote follow-up (visit 21) (~30–45min)

Questionnaire and Floodlight app assessments will be repeated at 4 months post-allocation and can be conducted remotely via phone with questionnaires returned via REDCap or post, if necessary.

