## Data collection and management

### Plans for assessment and collection of outcomes {18a}

#### Adverse events

AEs will be coded using the Medical Dictionary for Regulatory Activities (MedDRA), each AE will be counted once only for a given participant, presented by System Organ Class (SOC) and preferred term groupings. Details of any AEs will be collected using standardised case report forms and entered electronically into REDCap. The AE start date, stop date, severity, relationship, expectedness, outcome and duration will be recorded. To aid interpretation of AEs and secondary outcome measures, we will also collect data reporting concomitant medications or any changes to medications, recorded daily over the course of the intervention.

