### Plans to promote participant retention and complete follow-up {18b}

If a participant misses more than 3 consecutive intervention visits, they will be considered protocol non-compliant. These participants will be permitted to continue in the study until the end of the 5-week intervention phase, and remain in the study to complete follow-up safety and PROMs, but will be excluded from the follow-up MRI. Outcome measures are collected at the final intervention visit (face to face) and then again 4 months after group allocation. An automatic email is sent to remind participants to complete PROMs via REDCap. Additionally, participants will be contacted three times by two different methods before they are considered ‘lost to follow up’.

Protocol deviations will be monitored monthly by the trial management group and appropriate corrective and preventative actions taken to reduce incidence of protocol deviations. The statistical analysis plan will include per protocol analysis and intention to treat analysis for AE and participant-reported outcomes. As the follow-up MRI will only be conducted for participants without substantial protocol deviations, intention to treat analysis is not possible.

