### Adverse event reporting and harms {22}

#### Assessing

An AE is any untoward medical occurrence in a participant to whom a study intervention has been administered, including occurrences which are not necessarily related to or caused by the intervention. An AE can be any unfavourable or unintended sign, symptom or disease temporarily associated with study activities [54]. AEs will be recorded at each study visit and their severity and causal relationship assessed by the clinical PI. SAEs will be reviewed by an independent neurologist (see below).

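### The primary safety count closes with the last session's visit, and the protocol does not settle whether adverse events, relapses and medication changes are collected between then and the 4-month comparison

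*Protocol article*

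**What the plan says.** Outcomes {12}, Primary outcomes, defines the primary outcome as treatment-emergent AEs and SAEs "recorded at each visit during the intervention phase". The participant timeline identifies the intervention phase as visits 1 to 20 and gives its end: "Sessions will continue until 20 sessions are complete or up to a maximum of 5 weeks, whichever comes sooner". It also describes the questioning: on arrival each day, participants "will be asked if they are experiencing any symptoms that are out of the ordinary".

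Two other sections point to a longer collection period. Under Adverse event reporting and harms {22}, Assessing: "AEs will be recorded at each study visit and their severity and causal relationship assessed by the clinical PI". Under Plans to promote participant retention {18b}, participants who become non-compliant "remain in the study to complete follow-up safety and PROMs".

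The contacts after session 20 are described without an AE item. The section Visit 20 only lists questionnaires, app tests and an MRI done at visit 20 or within the following 2 weeks. The section on visit 21 says: "Questionnaire and Floodlight app assessments will be repeated at 4 months post-allocation and can be conducted remotely via phone".

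Medication changes are "recorded daily over the course of the intervention" (Plans for assessment and collection {18a}, Adverse events). The same section gives their purpose as helping to interpret AEs and secondary outcomes. Relevant concomitant care {11d} sets the same limit. The secondary outcomes include a comparison of symptom scores between arms at 4 months.

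**The concern.** The primary objective is whether a 20-session course is safe and tolerable. With questions asked on arrival, each of sessions 1 to 19 is normally followed by a later enquiry. Session 20, the point of greatest cumulative exposure, is followed by none that counts. A headache that evening or an event the next day is outside the primary outcome for every participant who completes the course.

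The 4-month comparison has a related weakness. MS relapse and disability progression are the protocol's own expected SAEs, and Reporting generally exempts expected events from immediate notification. Relapse, a change of disease-modifying therapy and high-dose steroids are also listed under {11b} as reasons a participant may no longer be fit to take part. If none of these is asked about between session 20 and visit 21, a difference in fatigue, mood or motor scores at 4 months cannot be separated from them. The gap would not show as missing either, because {20c} treats missing AE data as impossible.

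**Working it through.** The protocol gives no figure of its own on this point. The check is a comparison of the sections, followed by simple arithmetic on the follow-up time.

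**Step 1. The sections side by side**

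| Section | Period stated or implied | Item |
|---|---|---|
| Primary outcomes {12} | Visits 1 to 20 | AEs and SAEs that count as primary |
| Intervention phase | Visits 1 to 20, on arrival | Symptom question; AEs and medication changes daily |
| Assessing {22} | Each study visit, hence visit 21 if read literally | AE recording |
| Retention {18b} | Follow-up | Safety, for non-compliant participants |
| Visit 20 only; visit 21 | Up to 2 weeks after visit 20; 4 months after allocation | No AE or medication item named |
| {11d} and {18a} | The intervention | Medication changes |

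A counting window narrower than the recording window is coherent, so the first and third rows can both stand. What is unsettled is whether the two later contacts ask about AEs. Medication changes after the intervention are outside every period stated for recording them.

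**Step 2. Share of follow-up after the last session**

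Inputs:
- Four months = 4 × 365.25 / 12 = 121.75 days.
- Last session, counted from the first as day 0: day 25 (20 weekday sessions from a Monday start, 3 × 7 + 4) to day 35 (the 5-week maximum).
- Gap from allocation to first session: 0 to 14 days. This is an assumption; the protocol says only that allocation precedes the first intervention visit.

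Formula: share = (121.75 − gap − last session day) / 121.75.

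| Gap (days) | Last session (day) | Days after last session | Share |
|---|---|---|---|
| 0 | 25 | 96.75 | 79.5% |
| 0 | 35 | 86.75 | 71.3% |
| 14 | 25 | 82.75 | 68.0% |
| 14 | 35 | 72.75 | 59.8% |

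So about 73 to 97 days, or 60% to 80% of the 4 months, follow the last session.

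**Step 3. Illustration for relapse**

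The protocol gives no relapse rate. Assume 0.1 to 0.5 per person-year, with the 20 participants reported under Trial status. Expected relapses = 20 × rate × days / 365.25.

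- After the last session: 20 × 0.1 × 72.75 / 365.25 = 0.4, up to 20 × 0.5 × 96.75 / 365.25 = 2.6.
- During treatment: 20 × 0.1 × 25 / 365.25 = 0.1, up to 20 × 0.5 × 35 / 365.25 = 1.0.

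Under any one rate in this range, more relapses are expected after the last session than during treatment. The numbers are small, but so is the trial.

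**The case against.** The strongest reply is that the protocol describes two different things: which events count in the primary comparison, and when events are recorded. Recording more widely than one counts is ordinary practice. Visit 21 is a numbered visit, so the rule under Assessing covers it on its face. The schedule figure, where an AE row would normally appear, is not shown, and the article is a condensed account. This stands, and it limits the point in three ways.

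- A reader might infer that nobody is observed for safety after session 20. The documents do not support that. Assessing and {18b} imply later collection, SAE and SUSAR reporting has no stated end date, the MRI looks for new lesions up to 2 weeks later, and symptom scales are repeated at 4 months. Source data verification under {19} also covers relapses and concomitant medications, though its timing is not stated.
- A reader might infer that the independent review of SAEs within 3 to 7 days cannot operate after session 20. It can, on a spontaneous or clinician report; it then depends on unsolicited information.
- A reader might infer that medication changes are lost from the primary safety result. They were never part of it; their absence affects interpretation only.

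It is also fair that an on-treatment window suits acute effects. The protocol expects headache, dizziness, tingling and scalp discomfort to resolve soon after stimulation, and a longer window admits unrelated events.

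The reply does not reach two things. The primary window as worded leaves out reactions that begin after the participant leaves session 20, which are acute effects of the kind the window is meant to capture. And the stated recording period for medication changes stops well before an outcome that those data are meant to help interpret.

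**Conclusion.** The point holds in a limited form. As written, the primary outcome excludes events that arise after the visit for the last session, and the sections on AE, relapse and medication collection do not agree on what happens between then and visit 21. The interval is about 60% to 80% of the 4 months after allocation, given a last session on day 25 to 35 and an assumed allocation gap of 0 to 14 days. Those percentages describe the length of the interval, not the number of events lost: most acute reactions would be caught during treatment, and some later events would reach the record by other routes. If the schedule figure lists AEs at visit 21, the uncertainty about AE collection goes, but the primary window and the stated medication limit remain. This is a worthwhile, inexpensive clarification and does not undermine the primary comparison as a whole.

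**What to change.** 1. State the collection periods for AEs, SAEs, relapse and medication changes once, and bring {11d}, Primary outcomes {12}, the visit 21 section, {18a}, {18b} and Assessing {22} into line with that statement.
2. Count treatment-emergent AEs in the primary outcome to the same fixed number of days after the last session for every participant, ascertained at an existing contact or by a brief call. Do not tie the window to the MRI date: the scan may fall anywhere from 0 to 14 days after visit 20 and is not done for non-compliant participants, so the time at risk would differ between people.
3. Ask about AEs, SAEs, relapse and medication changes at visit 21, and list them as a separate follow-up period outside the primary count.
4. Trial status reports recruitment closed at 20, last visits expected by the end of December 2021 and no between-group analysis at submission. The window can therefore still be fixed before data lock. For participants already past these contacts, report the period without AE collection as a limitation and do not treat it as event-free.

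The cost is protocol wording, added questions on the case report form, and a short call for some participants. The downside is a few more unrelated background events in both arms, which the separate listing and a short fixed window keep small.

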## Objectives {7}

### Primary objective

To determine if low-intensity rTMS using an iTBS pattern, delivered across 20 sessions over a maximum of 5 weeks, is safe and tolerable for people living with MS.

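### The primary tolerability comparison ignores recurrence: a reaction at one session and a reaction at all 20 sessions score the same, and no other stated analysis separates them

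*Protocol article*

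**What the plan says.** The primary objective (Objectives {7}) is to find out whether low-intensity rTMS, "delivered across 20 sessions over a maximum of 5 weeks, is safe and tolerable for people living with MS". The schedule is repeated exposure with repeated enquiry: "Participants will attend 20 sessions over a period of 4 consecutive weeks"; on arrival each day they "will be asked if they are experiencing any symptoms that are out of the ordinary"; and "AEs and any concomitant medication changes will be recorded daily" (Intervention phase). An AE is any untoward occurrence, "including occurrences which are not necessarily related to or caused by the intervention" (Assessing, under Adverse event reporting and harms {22}).

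Under Primary outcomes, the arms are compared on "the proportion of participants that had at least one AE against participants who experienced no AEs (each participant counted once"). Statistical methods {20a} tests that proportion with Fisher's exact test. For the coded tables, the Adverse events section under {18a} says "each AE will be counted once only for a given participant". The same section says "The AE start date, stop date, severity, relationship, expectedness, outcome and duration will be recorded".

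The other stated safety and tolerability summaries are tests by severity level ({20a}), a table or listing of serious AEs and of AEs leading to discontinuation (Primary outcomes), and the proportion completing all 20 sessions (Protocol compliance).

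**The concern.** The Risks section describes the common side effects as mild and usually short-lived after stimulation, and the AE severity section lists headache, dizziness, tingling and scalp discomfort as expected. When such reactions follow a daily procedure, tolerability depends largely on how often they come back. The stated measure records only whether they ever occurred.

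At stake is the answer to the primary objective. Two arms could show the same any-AE proportion while participants in one react at most of their sessions and those in the other react once. The stated summaries also cannot show whether reactions fade or build up over the four to five weeks, although a 20-session study is well placed to show this.

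**Working it through.** **1. The plan's own figures.** Primary outcomes gives reference incidences from depression trials: headache 28% − 16% = 12 points, and scalp pain or discomfort 39% − 15% = 24 points. Both reproduce. The sample size of 30 has no power calculation to reproduce.

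**2. Does any stated analysis see repetition?** Take a participant with a mild headache after all 20 sessions who keeps attending, and compare with a participant who has one mild headache.

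- Any AE against none: both score 1.
- MedDRA tables: both contribute one headache.
- Tests by severity level: neither has a high-intensity AE, an SAE or a SUSAR. Both fall only in the general treatment-emergent category.
- Discontinuation listing: neither appears.
- Completion of 20 sessions: both count as complete.

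Nothing separates them.

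**3. How much can be hidden?** An illustration at the planned 20:10 split with 20 sessions each (the reaction counts are assumed):

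| | rTMS | Sham |
|---|---|---|
| Participants reacting | 6/20 = 30% | 3/10 = 30% |
| Sessions with a reaction, per reactor | 15 | 1 |
| Sessions affected | 6 × 15 = 90 | 3 × 1 = 3 |
| Sessions delivered | 20 × 20 = 400 | 10 × 20 = 200 |
| Share of sessions affected | 22.5% | 1.5% |

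The primary difference is 0 points. The burden per session differs by a factor of 15.

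**4. Is there also a ceiling effect?** With per-session risk q and independent sessions, P(any AE) = 1 − (1 − q)^20. The documents give no per-session rate, so q is assumed over a range, with the rTMS risk set at 2q. To allow for people who react repeatedly, a beta-binomial with within-person correlation ρ gives P(any AE) = 1 − B(a, b + 20)/B(a, b), where a = q(1 − ρ)/ρ and b = (1 − q)(1 − ρ)/ρ. Differences are in points and were taken before rounding.

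| Sham vs rTMS risk per session | Independent sessions | ρ = 0.3 |
|---|---|---|
| 1% vs 2% | 18.2% vs 33.2% (+15.0) | 5.6% vs 10.9% (+5.3) |
| 5% vs 10% | 64.2% vs 87.8% (+23.7) | 25.3% vs 44.5% (+19.3) |
| 10% vs 20% | 87.8% vs 98.8% (+11.0) | 44.5% vs 70.2% (+25.6) |
| 15% vs 30% | 96.1% vs 99.9% (+3.8) | 59.1% vs 84.5% (+25.4) |
| 20% vs 40% | 98.8% vs 100.0% (+1.1) | 70.2% vs 92.3% (+22.1) |

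Solving (1 − q)^20 − (1 − 2q)^20 = 0.10 on the high side gives q ≈ 10.5%, with a sham any-AE proportion of 89%. Only above that does the ceiling bring a doubled risk below 10 points. The small difference in the first row at ρ = 0.3 comes from rare events, not from a ceiling.

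The reference incidences of 15% to 39%, if read as whole-course figures (an assumption), give q = 1 − (1 − 0.15)^(1/20) = 0.8% to 1 − (1 − 0.39)^(1/20) = 2.4%. Headache and scalp pain combined, if independent, give 1 − 0.84 × 0.85 = 29% for sham and 1 − 0.72 × 0.61 = 56% for rTMS. Neither is near a ceiling.

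**The case against.** The strongest reply has three parts.

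First, tolerability does not rest on the yes/no measure alone: severity, discontinuation and completion are also reported. This is fair for worse grades and for reactions that stop treatment. It does not reach mild reactions that recur in people who continue.

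Second, the article defers detailed methods to a statistical analysis plan that is not shown, and event-count tables often sit there. That is true, so one cannot say that the trial will yield nothing on tolerability by session. The point concerns what the article does fix: it states a counting rule in two places, and both remove recurrence.

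Third, the sentence on counting each AE once deals with coding and presentation by organ class and preferred term. A reader might infer that repeat occurrences will not be recorded. The text does not say so, and dates and duration are recorded. One clarifying sentence would settle it.

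A reader might also infer that 20 daily enquiries drive the any-AE proportion towards 100% in both arms and so shrink the difference towards acceptability. The documents do not support this as a general claim. It needs a sham risk above about 10.5% per session with independent sessions, while the reference reaction rates imply about 0.8% to 2.4% and the article expects lower rates here. Clustering within people removes most of the effect. The 10% limit is also set for adverse reactions, not for AEs of any cause. An open daily question about any cause could produce higher rates than the two reference reactions, so the ceiling remains a possibility, but only that.

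**Conclusion.** The point holds as a weakness in a stated counting rule. The primary comparison and the AE tables ignore recurrence, and no other analysis in the article restores it for mild reactions that do not end treatment. The possible size is large: equal proportions of 30% can stand beside session burdens of 22.5% and 1.5%. That example shows what the measure can miss. It does not predict the result, and it uses the planned 20:10 split, whereas Trial status says recruitment closed at 20 participants. The loss of information needs no assumption about saturation. Clustering of reactions in a few people, which weakens the ceiling argument, is the pattern in which recurrence is most fully hidden. The any-AE proportion remains a legitimate primary measure. It needs a companion.

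**What to change.** Under Primary outcomes, keep the any-AE proportion as primary and add a descriptive measure reported beside it. For each participant and arm, give the number of sessions with at least one AE, and separately with at least one related AE, divided by sessions delivered. Tabulate it by week and by maximum grade. In the Adverse events section under {18a}, state that counting once applies to the MedDRA incidence table only and that every occurrence is kept with its own dates.

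The cost is a few words and one table. The dates, grade and relationship it needs are already recorded, provided that recurrences were entered as separate occurrences or with dates that identify the sessions affected. That should be checked now, since recruitment has closed. The change can still be made before results are known: Trial status reports that no intervention comparisons had been run at submission, and the analysis plan is to be signed before data lock. The downside is one more descriptive safety measure to interpret in a small sample; it should carry no formal test.
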